**Ethics and dissemination:**

By standardising methods to evaluate dengue burden across several sites in Africa, these studies will generate evidence for dengue burden in Africa and data will be disseminated as publication in peer-review journals in 2018.

Strengths and limitations of this studyThere have not been population-based studies conducted with a multidisciplinary approach (ie, surveillance, healthcare utilisation and serosurvey in one catchment area population). Data from the passive surveillance will be used to calculate annual incidences of dengue and data from the serosurvey will estimate the force of infection and prevalence.The studies were conducted in three locations in Africa, based on standardised methods and laboratory algorithm. Thus, comparison by site would be possible.This is not a cohort study. The passive facility-based surveillance may lead to underestimation of the burden of dengue fever by measuring incidence based on only those that sought care at our study facilities.There may be limited generalisability of our study results to other dengue-endemic parts of Africa.

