**Figure 2 F2:**
[figure not shown]
Map of the study area in Ouagadougou, Burkina Faso.

Gabon, located on the west coast of Central Africa, has an area of nearly 270 000 square kilometres (100 000 sq. mi) with a population estimated at 1.5 million. Its capital and largest city is Libreville. In 2014, it is reported that 87% of the Gabonese population lived in urban areas.^28^ The sixth largest city, Lambaréné, the capital of Moyen-Ogooué province, is located 75 km south of the equator, with a population of 25 257 in 2009. The majority of Lambaréné residents live in semirural areas. About 42% of the Gabonese population is under 15 years of age.^29^ Similarly, Lambaréné’s population is relatively young with about 50% under 20 years of age.

The health services of Gabon are mostly public, but there are some private institutions as well. With one of the best medical infrastructure in the region, almost 90% of the population have access to healthcare services. Albert Schweitzer Hospital (ASH) is a private institution which served as a study site for the passive fever surveillance study.^30 31^ The study area in Lambaréné is shown in figure 3.

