### Study components

#### Fever surveillance—design and methods

To determine burden due to symptomatic dengue in each of the three sites in Burkina Faso, Gabon and Kenya, passive facility-based fever surveillance was implemented in a well-defined catchment area population. In Burkina Faso, the surveillance study was initiated in December 2014 in five selected primary healthcare centres, locally called ‘Centre de Santé et de Promotion Sociale’, in the municipality of Ouagadougou, with a catchment population of 105 000 residents. This project was implemented in collaboration with Centre Muraz in Bobo-Dioulasso, EQUITE sante programme (a collaborative programme between University of Montreal and Action-Gouvernance-Integration-Reinforcement, AGIR, based in Ouagadougou, funded by the Canadian Institute of Health Research) and DVI. In Gabon, the surveillance study was initiated in the ASH serving a catchment population of 130 000 residents in the Moyen-Ogooué and surroundings within Lambaréné, in collaboration with CERMEL and Institute of Tropical Medicine in Tubingen, Germany. In Kenya, the surveillance study was implemented at Ganjoni dispensary, Tudor subcounty Hospital and Coast Provincial General Hospital, serving a catchment population of 70 000 residents in Mombasa, in collaboration with Kenya Medical Research Institute and Ministry of Health of Kenya.

As described in figure 5, both outpatients and inpatients at the designated study facilities, who meet inclusion criteria as mentioned earlier were tested for dengue, first with SD Dengue Duo RDT. Dengue confirmation was done by detection of dengue virus in serum samples using PCR as well as antidengue IgM and IgG antibodies in acute and convalescent serum by ELISA (SD Dengue IgM & IgG capture ELISA tests, Standard Diagnostics, Yongin-Si, Korea).^10 37^ Every consecutive patient meeting inclusion criteria was eligible for enrolment during the study period. Infants<1 year old were not included due to operational limitations, such as difficulty of infantile bleeding.

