### Variables of the surveillance questionnaires

The variables collected are listed in table 1.

**Table 1 T1:** List of variables collected in the passive fever surveillance data collection form

Topic	Description	Items
Basic information	Demographic and basic information about the patient and the treatment received	Type of treatment, where patient is enrolled (IPD vs OPD) Date of fever onset, duration of fever Current temperature Tourniquet test results Patient’s address (district and village-level) Date of visit, date of birth, age and sex Weight and height
General health condition	Current condition of the patient (self-report) and underlying diseases of the patient	How well the patient could handle daily activities Pre-existing conditions
Signs and symptoms during this illness	A set of signs and symptoms that may be related to fever and dengue (dengue fever and dengue haemorrhagic fever) at both visits 1 and 2	Rash, fatigue, headache, retro-orbital pain, neck/ear pain, sore throat, breathing difficulty, cough, expectoration, gastrointestinal signs (nausea/vomiting, diarrhoea, abdominal pain and so on), haemorrhagic signs (nose/gum bleeding, ecchymosis, petechiae and so on), signs of shock (cyanosis, capillary refill), arthralgia, myalgia, loss of appetite, jaundice and so on
Medical history	Previous dengue-related or other flavivirus infection as well as vaccination history (self-report)	Previous dengue infection and related hospitalisation Previous infection to other commonly circulating arboviral infection in the area (ie, Yellow fever vaccination history)
Laboratory findings	Records from the routine laboratory tests widely used in clinical fever/dengue patient management, as part of the hospital care procedure	Platelet count, haematocrit, haemoglobin, leucocytes, neutrophils, protein level, AST, ALT, urine test results and so on
Clinical diagnosis	Clinician’s diagnosis with or without referring to the RDT	Diagnosis given by the physician based on clinical presentation after physical examination of the patient
Dengue testing results	Results from the dengue tests, mainly RDTs for dengue as well as other commonly circulating arbovirus in the area	Dates of blood draw Test results of the RDT IgM/IgG capture ELISA results PCR results (if available)
Treatment	Medicine(s) prescribed and the starting and end dates	Antibiotics, paracetamol, ibuprofen, aspirin and others that may be site-specifically prescribed

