Outcome	Outcome of this particular visit	Hospitalised, returned home or referral
Hospitalisation	Information collected only among hospitalised patients in the surveillance to record other severe signs and progression of illness	Admission and discharge diagnoses Presence of haemorrhagic signs or shock syndrome
Hospital charges	Expenses and hospital charges incurred by patient on the visit 1	Amount of the out of pocket payment by the patient or the family/or guardian Breakdown of the hospital charges (laboratory, medication, admission-related charges)
Final outcome	Outcome of the patient’s illness at the second visit	Final diagnosis given for the patient, outcome of illness Completion of study participation (early termination and the reason and so on)

ALT, Alanine AminoTransferase; AST, Aspartate aminotransferase; IPD, Inpatient department; OPD, Outpatient department; RDT, Rapid Diagnostic Test.

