As outpatient disease accounts for the greater part of dengue disease burden, clinical profile of individuals with DENV infection will be characterised by the type of treatment (hospitalised vs outpatients) as well as by severity of the disease (severe vs non-severe by the 2009 WHO criteria).^46^ Classification is determined after the course of illness is completed (typically during the convalescent visit). Symptomatic dengue is classified as outpatient or hospitalised. Progression of dengue is recorded as DF, DHF I, DHF II, DHF III or DHF IV, and clinical patterns will be compared by the severity grade.^46 47^ These will be compared with results obtained from other DVI studies in Latin America (Colombia) and Asia (Thailand, Vietnam and Cambodia). Overall, comparisons will be made across Burkina Faso, Gabon and Kenya.

With the age-stratified sera that reflect the age distribution of the general population of the country, the serological survey sampling strategy ensures sufficient subjects to obtain precise age-specific estimates of seropositivity and seroconversion of the catchment area population. The seroconversion rate and change in the immune status will be determined by age group during the study period. The age-stratified serosurvey data will also allow calculation of the force of infection of dengue in the study population. After enrolment, there are subjects who drop out in the follow-up bleeds about 6 months later. Basic demographic information will be compared between those that completed participation and those with incomplete participation to check whether study subjects represent the catchment area population. Comparisons will be made among Burkina Faso, Gabon and Kenya.

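### Surveillance enrols at different levels of care in the three countries, so planned cross-country comparisons of hospitalisation, severity and clinical profile may reflect enrolment setting

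*Protocol article*

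**What the plan says.** All references are to the protocol article.

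- **Where cases are found.** In Burkina Faso, surveillance ran "in five selected primary healthcare centres" (Fever surveillance—design and methods). In Gabon it ran in one hospital, which "is a private institution which served as a study site for the passive fever surveillance study" (Study area and population). In Kenya, "the surveillance study was implemented at Ganjoni dispensary, Tudor subcounty Hospital and Coast Provincial General Hospital" (Fever surveillance—design and methods).
- **What is described.** Planned statistical analysis classes symptomatic dengue as outpatient or hospitalised. It profiles cases by that split and by severe versus non-severe disease, and compares clinical patterns by severity grade from DF to DHF IV.
- **What is compared.** The same paragraph plans a comparison with the programme's studies in Colombia, Thailand, Vietnam and Cambodia, and then states: "Overall, comparisons will be made across Burkina Faso, Gabon and Kenya".
- **Why comparison is thought valid.** The strengths and limitations box cites standardised methods and a common laboratory algorithm: "Thus, comparison by site would be possible".
- **What is recorded.** Table 1 has a visit outcome of "Hospitalised, returned home or referral". Its laboratory item is described as "Records from the routine laboratory tests widely used in clinical fever/dengue patient management, as part of the hospital care procedure".

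**The concern.** Questionnaires and assays are standardised, but the level of care at which patients enter is not. A primary centre and a hospital draw different mixes of mild and serious illness from the same population. If the three countries had identical dengue, the enrolled cases could still differ in the proportion hospitalised, the severity grades and the symptoms.

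At stake is how the clinical results are read. The Discussion says the clinical findings could guide case detection and management. A difference produced by the choice of facility could be taken as a difference between countries, or between Africa and the programme's sites elsewhere. The article describes no facility levels for those other sites, so like-with-like cannot be checked there either.

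**Working it through.** **Step 1. Can level of care be separated from country?**

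| Country | Primary-level facility | Hospital |
|---|---|---|
| Burkina Faso | five centres | none named |
| Gabon | none named | one, private |
| Kenya | one dispensary | two (subcounty, provincial general) |

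Burkina Faso and Gabon share no level. A term for level in a model comparing them would be the country term under another name, so no later analysis plan can separate the two. Only Kenya spans levels.

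**Step 2. Does a stated safeguard cover it?**

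- *Healthcare utilisation and refusal adjustments.* Planned statistical analysis applies them to the numerator of the incidence. The Discussion describes the inverse probability weighting as part of the incidence calculation. Neither is stated for the severity or symptom comparisons.
- *Inpatient versus outpatient covariate.* It belongs to the logistic model of dengue against non-dengue fever, not to a comparison of sites. It is also one of the characteristics being described, so it cannot stand in for level of care.
- *Limitations.* The Discussion names time frame, geography, care sought elsewhere, other diagnoses, cross-reactivity and participation. Facility level is not named.

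**Step 3. How large could the effect be?** The plan gives no figure for this comparison, so there is none to reproduce. The following is an illustration.

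Let *s* be the true hospitalised share among medically attended dengue, the same in both countries. Let *h* and *o* be the probabilities that a hospitalised case and an outpatient case are captured at the study facilities.

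Observed share = *s·h* / (*s·h* + (1 − *s*)·*o*)

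Assumptions, none from the documents: *s* = 0.10 and *o* = 0.50 at both sites, so the outpatient term is 0.90 × 0.50 = 0.45.

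| *h*, primary centres | *h*, hospital | Observed, primary centres | Observed, hospital | Ratio |
|---|---|---|---|---|
| 0.50 | 0.50 | 0.05/0.50 = 10.0% | 0.05/0.50 = 10.0% | 1.0 |
| 0.30 | 0.60 | 0.03/0.48 = 6.3% | 0.06/0.51 = 11.8% | 1.9 |
| 0.10 | 0.90 | 0.01/0.46 = 2.2% | 0.09/0.54 = 16.7% | 7.7 |

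The observed odds equal the true odds multiplied by *h/o*. The distortion therefore vanishes only if *h/o* is the same at both sites.

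**Step 4. Let outpatient capture differ too.** Take a true severe share of 5% everywhere, with capture probabilities again assumed.

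- Primary centres, severe 0.1 to 0.2 and non-severe 0.4: 0.005/0.385 = 1.3% to 0.010/0.390 = 2.6%.
- Mixed facilities, 0.4 for both: 5.0%.
- Hospital, severe 0.6 and non-severe 0.3 to 0.1: 0.030/0.315 = 9.5% to 0.030/0.125 = 24.0%.

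The direction is the same as in Step 3 whenever a hospital captures serious cases, relative to mild ones, better than a primary centre does.

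**The case against.** The best defence is that the text does not go as far as a reader might take it.

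- **The hospitalised share is not named as a compared quantity.** The plan speaks of clinical profile by treatment type and patterns by severity grade, which can be read as descriptions within strata. This is right as to wording. But the sentence on comparing the three countries follows directly with no restriction, and profiles within strata are themselves shaped by who reaches each facility.
- **Hospitalised cases are not ruled out in Ouagadougou.** A reader might infer that inpatients cannot appear there, or that severe dengue would be near zero by design. The documents do not support that. Classification is made once the illness has run its course, and Table 1 records referral and a final outcome. A patient enrolled at a primary centre and later admitted elsewhere could be classed as hospitalised. Patients who go straight to a non-study hospital are the ones missed.
- **Poorer grading at primary centres is not shown.** A reader might infer it from the laboratory item in Table 1. No availability by site is given, and haemorrhagic and shock signs are on the general form. It is a matter to check.
- **Partial disclosure.** The article admits that incidence rests on those who sought care at study facilities. That concerns under-ascertainment of incidence, not a shift in case mix between sites.
- **The 7.7-fold figure is an extreme.** It rests on 10% versus 90% capture, and equal capture gives no difference. It belongs only at the end of a range.

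The confounding of level with country, and the lack of a safeguard for the clinical comparisons, stand after all of these.

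**Conclusion.** The concern holds, confined to hospitalisation, severity mix and clinical profile. As planned, the comparison between Burkina Faso and Gabon cannot tell country from level of care. The comparisons with Kenya and with the programme's other studies are open to the same distortion unless like settings are matched.

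The size cannot be fixed from the documents. Under the assumptions of Step 3, the apparent ratio runs from 1.0 to 7.7, with 1.9 at an intermediate set of capture fractions. The conclusion rests on the facilities named in the article and on no unreported hospital taking part in Ouagadougou.

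Incidence comparisons, which have their own utilisation adjustment, and serosurvey comparisons, which do not depend on facility enrolment, are outside this point.

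**What to change.** 1. In Planned statistical analysis, report hospitalisation, severity and clinical profile by site and facility level, descriptively. Draw no between-country or cross-programme inference from them, except between like settings where these exist. Stratifying by level will not rescue the Burkina Faso–Gabon contrast, because they share no level.
2. For Ouagadougou, report referral together with hospitalised from the Table 1 outcome field. State that patients who go straight to non-study hospitals are not captured.
3. Show, for each site, how many cases have the laboratory results needed for grading.
4. Qualify the comparability statement in the strengths and limitations box by naming facility level as a limitation.

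This changes wording and tables and uses fields already collected. The cost is a narrower cross-site claim, with fewer cases in any remaining like-with-like comparison.

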Wichmann *et al* calculated an expansion factor for children by comparing data from three cohort studies to national surveillance data in Southeast Asia.^33^ For children in Thailand, the age-specific expansion factors calculated were 11.85 for <5 years, 8.76 for 5–9 years and 7.81 for 10–14 years.^33^ The results show that, even for Asia where better reporting and surveillance systems are available, there is a considerable degree of under-reporting. For Africa, there may be more dengue cases under-ascertained (not seeking care) and under-reported (not reported even if a patient with dengue seeks care, given that dengue is not one of the routinely notifiable diseases in Africa), but such information on the extent of underestimation of dengue was not available.^34 35^ Also, the incidence estimates used in our sample size calculations were not from population-based studies. While it would have been ideal to adjust the incidence further for likely underestimation, the annual incidence used in sample size calculations could not be adjusted for possible under-reporting due to the lack of data. The sample sizes were calculated with 95% confidence levels and a margin of error at a fixed significance level within 25% of the true proportion of incidence. This gives relative precision of 75%, considering the gap in evidence for dengue incidence in the study areas. The final sample sizes were calculated by assuming 10%–20% (variable by site) non-response rate or loss to follow-up. The required catchment population size for the fever surveillance study in Burkina Faso was estimated to be 100 000, Gabon to be 77 000 and Kenya to be 70 000. In these catchment populations, the number of enrolled subjects depends on the number of eligible patients who seek care at the study facilities. How many eligible febrile episodes would actually present at our study facilities was difficult to predict; but after assessment of the volume of febrile patients at the facilities, a realistic upper limit for enrolment for a study period of approximately 1.5 years was set at 3000 subjects to offer enrolment to all consenting eligible patients.

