For the serological survey, the sample size was calculated similarly using the prevalence proportion based on published literature. Seroprevalence of 0.304 for Burkina Faso,^15^ 0.123 for Gabon,^21^ and 0.144 for Kenya^36^ were used. With the same confidence levels and allowed margin of error and assuming 10%–30% (variable by site) non-response rate, the sample size was calculated to be 3000 participants at each site. Again, with the scarcity of data from the selected countries, there were no other prevalence estimates reported or estimates from different age groups. As prevalence is expected to increase with age and higher prevalence would give a smaller sample size, our calculations are likely to be conservative.

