#### Serological survey—design and methods

While the facility-based fever surveillance studies provide estimates of the burden of medically attended dengue disease, evaluation of all DENV infections in a population—including subclinical and mildly symptomatic infections, which impact immune status—is needed to capture the overall impact of dengue. As part of the study package, population-based serological surveys were conducted in the same catchment population used for the fever surveillance. At each of the three sites in Africa, the serosurvey was conducted on a cohort of approximately 3000 randomly selected residents of urban and semiurban parts of Ouagadougou, Lambaréné and Mombasa. Without individual-level census information on all residents of Lambaréné and Mombasa, with help of community/village health workers, randomisation was done based on neighbourhoods (or defined areas for which the health workers/volunteers are responsible) as cluster units. As the community/village health workers are familiar with the villages and their residents, they are good entry points into the communities. With these health workers, the field team screened houses in the selected villages by knocking on doors of every 5–7 houses, depending on the household density per neighbourhood. Also, demographic information collected in previous research projects conducted in the same area was used as a guide, if available. In the case of the site in Ouagadougou, HDSS data were available and the EQUITE SANTE, a CIHR funded research programme of the University of Montreal, had set up a geographic information system database of houses in the study area. Using these data, households of potential enrolees of the serosurvey were preselected randomly and household visits were made in Ouagadougou. In the three sites, about 45% of the serosurvey samples were targeted to be collected from children 1 to 14 years of age, and 55% were targeted to be collected from adults between 15 and 55 years of age to reflect the age distribution of the general population of the area. Household-based enrolment was offered to the head of the household until the specific cap for the age-group was reached in Lambaréné and Mombasa.

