#### Healthcare utilisation survey

As the passive fever surveillance was conducted at study facilities, patients with potential dengue could be missed if they seek care elsewhere. To identify the proportion of fever and dengue cases potentially missed by the passive surveillance system due to patients living in the study area but seeking care outside of study facilities, a population-based healthcare utilisation survey was conducted in 400 randomly selected households from the study catchment area to characterise the healthcare utilisation patterns of the households when they have (self-reported) febrile episodes among the family members. In addition to assessing health-seeking behaviours of the residents, preferences in terms of health-seeking behaviour and respective reasons for their preferences were investigated. The questionnaire was administered to 400 heads of households. Among 3000 residents who participated in the serosurvey, there were about 600 households. From these households, 400 heads of households were randomly selected and offered enrolment in the health utilisation survey. Heads of households or a senior representative within the household were asked questions on health seeking patterns of their family members.

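### The serosurvey is said to guarantee precise age-specific seroconversion, but only overall seroprevalence was sized, and under stated assumptions each age band yields too few seroconversions

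*Protocol article*

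**What the plan says.** Planned statistical analysis claims that "the serological survey sampling strategy ensures sufficient subjects to obtain precise age-specific estimates of seropositivity and seroconversion of the catchment area population". The same section plans seroconversion by age group and comparisons among the three countries.

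The sizing is in Sample size. The fever surveillance is sized at 95% confidence with a 25% relative margin. The serosurvey takes over both settings, allows for 10–30% non-response depending on the site, and starts from published prevalences: "Seroprevalence of 0.304 for Burkina Faso,^15^ 0.123 for Gabon,^21^ and 0.144 for Kenya^36^ were used". The result is one figure for all three countries, for which the article reports that "the sample size was calculated to be 3000 participants at each site". No seroconversion rate, expected event count, age-group precision or design effect is given.

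Serological survey—design and methods controls age in two bands: "about 45% of the serosurvey samples were targeted to be collected from children 1 to 14 years of age", with the other 55% aged 15–55. In Lambaréné and Mombasa, "randomisation was done based on neighbourhoods (or defined areas for which the health workers/volunteers are responsible) as cluster units"; in Ouagadougou, households were preselected at random from existing databases. Healthcare utilisation survey adds: "Among 3000 residents who participated in the serosurvey, there were about 600 households". Bleeds are about 6 months apart: two each in Gabon and Kenya, four in Burkina Faso.

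**The concern.** Seroconversion can be seen only in people who are seronegative at baseline, and only over the time between bleeds. A sample that is ample for a prevalence of 12–30% can therefore be far too small for a six-month risk below 1%. The sentence treats the two quantities as equally secure, although only prevalence was sized.

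Age-specific seroconversion, and differences between ages or countries, could rest on a handful of events while being presented as precise. The Discussion expects the burden data to inform decisions on vaccine introduction, so readers may give such differences weight that they cannot bear.

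**Working it through.** **1. The plan's own figure.** For a 25% relative margin, n = 1.96²(1−p)/(p × 0.25²). This gives 141 (p = 0.304), 439 (0.123) and 366 (0.144). Dividing by 0.9 to 0.7 for 10–30% non-response gives 157–202, 487–627 and 406–522, so 3000 is not reproduced from the stated inputs. At n = 3000 under simple random sampling, overall seroprevalence would have relative half-widths of about ±5%, ±10% and ±9%. That quantity is well served, but this says nothing about seroconversion.

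**2. Inputs for seroconversion.** From the document:
- 3000 per site, hence 1350 children (45%) and 1650 adults (55%)
- the three sizing prevalences
- an interval of about 6 months
- for Gabon, a source age of about 30 months for the 12.3% (Site selection)

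Assumed here:
- constant force of infection λ with zero prevalence at birth (Sample size states this rule for the fever surveillance)
- uniform ages within bands (1 to under 15, 15 to under 56)
- retention of 80–100% (the document gives no drop-out rate)
- no clustering

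**3. Formulae.** The seronegative share is S = (e^(−λ) − e^(−15λ))/(14λ) in children and (e^(−15λ) − e^(−56λ))/(41λ) in adults. λ is chosen so that 0.45(1−S_child) + 0.55(1−S_adult) = p. Events = band size × S × (1 − e^(−λ/2)) × retention. Relative half-width ≈ 1.96/√events, which is rough below about 10 events.

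| Reading | λ per year | Seronegative children / adults | 6-month risk | Events at 100%: child + adult | Events at 80%: child + adult |
|---|---|---|---|---|---|
| Burkina Faso | 0.0174 | 1178 / 910 | 0.86% | 10.2 + 7.9 = 18 | 8.1 + 6.3 = 14 |
| Gabon | 0.0059 | 1288 / 1343 | 0.29% | 3.8 + 3.9 = 8 | 3.0 + 3.2 = 6 |
| Kenya | 0.0070 | 1277 / 1291 | 0.35% | 4.5 + 4.5 = 9 | 3.6 + 3.6 = 7 |
| Gabon, 12.3% at 30 months: λ = −ln(0.877)/2.5 | 0.0525 | 907 / 308 | 2.59% | 23.5 + 8.0 = 31 | 18.8 + 6.4 = 25 |

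| Reading | Half-width overall | Half-width by band |
|---|---|---|
| Burkina Faso | ±46–52% | ±61–78% |
| Gabon | ±71–79% | ±99–113% |
| Kenya | ±65–73% | ±92–104% |
| Gabon at 30 months | ±35–39% | ±40–45% children, ±69–78% adults |

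**4. Burkina Faso pooled.** May–June 2015 to January 2017 is about 1.6 years. The risk is 1 − e^(−0.0174 × 1.6) ≈ 2.7% of 2088 seronegatives, or about 57 events at full retention and 46 at 80%. That is ±26–29% overall. The bands hold about 26–32 children and 20–25 adults, or ±35–44%.

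**5. Against the protocol's margin.** A 25% half-width needs (1.96/0.25)² ≈ 62 events per band. Varying λ freely with all 3000 retained, one 6-month interval yields at most about 35 events in children (λ near 0.18) and 9 in adults (λ near 0.03), because higher transmission leaves fewer seronegatives.

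**6. Seropositivity, same model, before clustering.** Child and adult half-widths are ±14% and ±5% (Burkina Faso), ±24% and ±10% (Gabon), and ±22% and ±9% (Kenya). All are within 25%.

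**7. Clustering.** 3000/600 is about five participants per household. Any positive within-household or within-neighbourhood correlation widens all these intervals. The document gives no correlation, so no factor is applied.

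**The case against.** **The counts are model-based.** A reader might infer that the protocol's own inputs fix them. They do not: retention, the age distribution and the ages behind the Burkina Faso and Kenya prevalences are not stated. Holding Gabon's 12.3% at every age while using the 30-month λ would give 68 events. That conflicts with the protocol's own expectation that prevalence rises with age, and a split of roughly 31 and 37 would still exceed ±30% in each band. The bound in step 5 does not depend on the input prevalence, though it does assume a constant force of infection.

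**Six months is an unfavourable window.** This stands in part. The plan speaks of the study period, and pooling helps Burkina Faso (step 4). Kenya's second bleed ran from November 2016 to February 2017 after a May 2016 baseline, so a 9-month interval would raise 7–9 events to about 11–13. Bleeds around the rainy season, or an outbreak, could give more. None of this can be guaranteed in advance.

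**Stronger readings that the document does not support.** A reader might infer that seropositivity fails too; step 6 shows that, before clustering, it does not in the two sampled bands. A reader might infer that simple binomial intervals are planned. The article names no interval method, which may be left to the full protocol or analysis plan. A reader might also infer neighbourhood clusters at every site, but they are documented only for Lambaréné and Mombasa.

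**The sample is fixed.** Fieldwork ended in 2017, so only claims, analysis and reporting can change.

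**Conclusion.** The assurance is wrong as written for age-specific seroconversion. The only sizing shown is for overall prevalence. Under the declared assumptions, a single interval gives 6–18 seroconversions per site, or 25–31 in Gabon on the 30-month reading, with band-level half-widths of about ±40–113%. Even Burkina Faso's pooled follow-up misses the protocol's 25% margin by band. The exact counts depend on the assumptions. The shortfall in a single interval holds for any constant force of infection, even with full retention and no clustering; a strongly epidemic season is the exception. The conclusion is confined to seroconversion.

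**What to change.** - Remove seroconversion from the assurance in Planned statistical analysis. State its expected counts and precision by site and age band, with the assumptions declared.
- Report seroconversion among baseline seronegatives primarily as one rate per site, with Burkina Faso pooled over its three intervals. Make the two sampled age bands secondary, and describe comparisons between ages or sites as imprecise.
- Base age-specific force of infection on age-specific baseline seroprevalence. The plan already intends to derive it from the age-stratified survey data.
- Compute serosurvey intervals that allow for the documented sampling: neighbourhood and household in Lambaréné and Mombasa, household in Ouagadougou.

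The cost is wording and analysis only. Intervals become wider, and age-specific seroconversion moves to secondary status.
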